## Abstract

**Background:**

Interventions to delay or prevent the onset of rheumatoid arthritis (RA) have attracted much attention in recent years. Researchers are now exploring various prevention strategies but no unified consensus was reached. A traditional Chinese medicine (TCM) prescription, Formulation A (FA), may be potential to reduce the risk of RA development.

**Methods:**

This is a multicenter, double-blind, placebo-controlled, randomized clinical trial. We will enroll 72 participants who are positive for anti-cyclic citrullinated peptide (anti-CCP) antibody but without synovitis. Participants will be randomly assigned to either FA or placebo for 52 weeks. All will then undergo 52 weeks of observation. The primary outcome is the time interval between the study entry and RA diagnosis. The secondary outcomes include the proportions of RA diagnosis, anti-CCP antibody, rheumatoid factor (RF), the high-sensitivity C-reactive protein (hs-CRP), the erythrocyte sedimentation rate (ESR), the 28-tender joint count (TJC28), the 28-swollen joint count (SJC28), morning stiffness time, the visual analog scale (VAS), Patient’s Global Assessment (PtGA), Physician’s Global Assessment (PGA), Health Assessment Questionnaire (HAQ), Generic Quality of Life Inventory-74 (GQOLI-74) scores, and ultrasound images of joints.

**Discussion:**

This study attempts to test the feasibility of a clinical trial using FA in RA prevention. It will lay the foundation for future research and ensure validity.

## 1 Introduction

Rheumatoid arthritis (RA) is one of the most common autoimmune diseases worldwide which can lead to severe joint damage by causing inflammation of synovium. Extra-articular manifestations are also common, and overall, the disease causes high social and economic losses (1).

Although awareness of early diagnosis, treat-to-target strategies, and the latest biologic agents have led us into a new era of RA treatment, we should continue to focus on disease prevention. Therefore, researchers have proposed recommendations on preclinical RA (pre-RA) and clinically suspect arthralgia (CSA) to help identify individuals at risk of developing RA (2, 3).

However, finding the most appropriate drugs and therapies for high-risk individuals is not easy. The causes of the disease are multiple and complex (4). And the concepts and descriptions of the at-risk stage of RA are still evolving (2). Both genetic and environmental factors contribute strongly to the development of RA, leading to epigenetic and posttranslational modifications, which in turn trigger autoimmune responses through the activation of immune cells and the formation of autoantibodies (5, 6). The at-risk stage can be recognized as the period with some clinical manifestations until the onset of clinical arthritis. Years before the onset of RA, anti-cyclic citrullinated peptide (anti-CCP) antibodies are frequently found (7). Musculoskeletal manifestations, such as arthralgia, bone loss and fatigue, are also common (8). When these at-risk individuals are also ever smokers and carriers of genetic risk alleles, the risk of developing RA increases more than 20-fold (9). These existing at-risk cohorts have been recently summarized (10). They could be the target of the current prevention trial (11).

Since the mechanisms of RA pathology involve multiple immune cells, effector cells, and stromal cells and many different intracellular signaling pathways, a drug or a combination of active compounds with a wide range of actions might be preferable. Can TCM be useful and provide effective solutions for RA prevention? Previous studies have shown that TCM can lead to a decrease in the levels of rheumatoid factor (RF) and anti-CCP (12), reduce bone damage (13) and achieve a strong therapeutic effect (14), which could be a potentially effective choice for RA prevention.

TCM has been applicated in clinical settings in China for millennia. Formulation A (FA), known as Yiqi-Qushi-Fangbi-Fang (YQFF) in the Chinese nomenclature, has been selected for its role in RA prevention in clinical practice. FA consists of eight different common Chinese herbs, as shown in Table 1 (11). It shows the potential to alleviate joint symptoms, such as pain, numbness, stiffness, distension, swelling, limb flexion and extension, so as to decrease the risk of RA.

**TABLE 1 T1:** Components and their names in formulation A.

Chinese	Pinyin	Scientific name	Latin name	Officinal parts	Doses
薏苡仁	Yiyiren	Coix lacryma-jobi var. ma-yuen (Rom.Caill.) Stapf	Semen Coicis	Seed	30 g
当归	Danggui	Angelica sinensis (Oliv.) Diels	Radix Angelicae Sinensis	Root	10 g
白芍	Baishao	Paeonia lactiflora Pall.	Radix Paeoniae Alba	Root	10 g
麻黄	Mahuang	Ephedra sinica Stapf	Herba Ephedrae	Stem	3 g
桂枝	Guizhi	Cinnamomum cassia Presl.	Ramulus Cinnamomi	Branch	10 g
黄芪	Huangqi	Astragalus mongholicus Bunge	Radix Astragali seu Hedysari	Root	30 g
苍术	Cangzhu	Atractylodes lancea (Thunb.) DC.	Rhizoma Atractylodis	Root, stem	15 g
炙甘草	Zhigancao	Glycyrrhiza uralensis Fisch.	Radix Glycyrrhizae	Root, stem	15 g

In fact, FA represents a synthesis and innovative adaptation of two distinguished TCM formulas, Huangqi-Guizhi-Wuwu-Tang (HGWT) and Yiyiren-Tang (YYRT).

The application of HGWT for the treatment of RA in China has a long history. Modern pharmacological studies have shown that monoterpenoids, flavonoids, organic acids, triterpenes, amino acids, gingerols, alkaloids, and glycosides are the main chemical components in HGWT (15–17). It has anti-RA effects by targeting multiple pathways (18), such as regulating neurotransmitters (19); adjusting macrophages and the levels of inflammatory cytokines (20); decreasing the mRNA and protein levels of p-NF-κB and IL-17 (21); reducing inflammation in fibroblast-like synoviocytes (22); and synergistically targeting the cAMP, PI3K/Akt, and HIF-1α pathways (23). In addition, HGWT is widely used in treating neurological disorders, such as neuropathic pain (24), peripheral neuropathy (25–27), peripheral neurotoxicity (28, 29), and stroke rehabilitation (24).

YYRT has adjuvant therapeutic value for RA through diverse anti-inflammatory and immunomodulatory effects. Coix seeds, the main component of YYRT, contain coix seed ester and polysaccharide components, which can exert anti-RA effects by reducing the levels of proinflammatory cytokines (IL-1β, TNF-α, IL-6, and MCP-1), alleviating oxidative stress (30), and alleviating synovial angiogenesis by suppressing the HIF-1α/VEGF-A signaling pathway (31). A compound study revealed that YYRT might improve the treatment effect against RA, particularly the cold-dampness obstruction type (32).

FA, the combination of HGWT and YYRT, broadens the application spectrum of TCM therapeutic approaches. Its ingredients contain anti-inflammatory and immune-regulating components, making it suitable for the high-risk stage of RA. Also, it has a more palatable taste, which can significantly improve patients’ medication adherence. However, there is a lack of high-quality evidence-based studies on FA. Thus, we outline an ongoing multicenter clinical trial to explore its role in RA prevention.

## 2 Methods and analysis

### 2.1 Objectives

This study aims to evaluate the feasibility of a multicenter clinical trial of FA for RA prevention.

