#### 2.5.2 The primary outcome

The primary outcome is the time to the occurrence of RA. It is defined as the time interval from inclusion to the occurrence of RA. RA occurrence refers to the confirmation of arthritis or synovitis by ultrasound and meeting the 2010 ACR/EULAR RA classification criteria.

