### 2.7 Sample size

As this trial primarily assessed feasibility on RA prevention by TCM, sample size was not strictly predetermined. We initially allocated 30 participants per group with an additional 20% potential dropouts, resulting in a total of 72 recruitment. Nevertheless, we provide a formal calculation for reference purposes.

According to previous study (35), we assumed that RA incidence would be 20.0% in the FA group and 37.5% in the placebo group. This allocation ensured an power of over 80%. Calculation was in accordance with the formula of Chow (36) as follow:

$$\text{N}=\frac{{\left({\text{Z}}_{\alpha }+{\text{Z}}_{\beta }\right)}^{2}\,\left[{\text{P}}_{0}\,\left(1-{\text{P}}_{0}\right)+{\text{P}}_{1}\,\left(1-{\text{P}}_{1}\right)\right]}{{\left(\varepsilon +\delta \right)}^{2}}$$

Note: *N* is the sample size of each group. P_0_ and P_1_ are the RA incidence in the FA group and placebo group, respectively. For a two-sided test, α = 0.05, β = 0.2, 1−β = 0.8, Z_α_ = 1.96, Z_β_ = 0.84. The superiority margin δ = 0.15. And ε is the practical margin.

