#### 2.9.2 Statistical methods

Data analysis will be conducted by statisticians who are independent of the research team. All analyses are performed via the SPSS software (IBM SPSS Inc., Armonk, NY, USA). An intent-to-treat analysis will be carried out for participants who receive treatment at least once. Missing data will be imputed in accordance with the principle of multiple imputations. Continuous variables will be imputed using linear regression models, while categorical variables will be imputed using logistic regression models. Multiple imputation was performed with a user-defined number of MCMC (Markov Chain Monte Carlo) iterations. Per-protocol analysis is limited to participants who strictly adhere to the protocol and complete the trial. All the statistical tests are 2-sided, and differences are considered statistically significant at *P* values less than 0.05.

The safety dataset will also include all patients who received ≥1 dose of the intervention. The primary outcomes will be compared between the two groups via the log-rank test and the Kaplan–Meier method, and superiority will be considered with a 95% confidence interval. The secondary outcomes will be presented as frequencies, means, standard deviations (SDs), medians and ranges. To determine treatment effects, changes in the above outcomes from baseline will be analyzed via ANOVA. Group effects and influencing factors will be analyzed via analysis of covariance or a logistic regression model with covariates including sex, age, concomitant medication and measurements at baseline. Subgroup analyses will not be performed to avoid insufficient statistical power because of the small sample size. Safety will be evaluated through tabulations of AEs and coded based on the Chinese version of the Medical Dictionary for Regulatory Activities (MedDRA). Safety data will be presented with descriptive statistics at baseline, 52 weeks and 104 weeks for each group.

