## 4 Discussion

Although previous studies have tested the use of DMARDs to delay the onset of RA (37, 38), there is also a growing need for clinical evidence for TCM.

However, this trial has several potential limitations. It is a small-scale pilot trial, and therefore, the results may not be conclusive or sufficiently generalizable. Nevertheless, any significant differences or trends in the efficacy of FA at the endpoints of this trial will provide seminal evidence for the search for RA prevention, and even neutral results will be important revelations to the community. RA is a serious global rheumatic disease that affects many people both physically and mentally.

With the rapid advances in science and medicine in recent years, remission is no longer the only goal to meet the needs of RA patients. Medical care and management strategies for at-risk individuals are becoming a priority for clinicians and researchers. This trial can provide high-quality data and hopefully suggest a new therapy to prevent rheumatoid arthritis.

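### The stated objective is feasibility, but every listed outcome is efficacy or safety, and the primary superiority test has about 34–40% power, not over 80%

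*Protocol article*

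**What the plan says.** Feasibility is the only objective in section 2.1: "This study aims to evaluate the feasibility of a multicenter clinical trial of FA for RA prevention". The abstract's Discussion says the same ("This study attempts to test the feasibility of a clinical trial using FA in RA prevention"), and section 2.7 uses it to justify the sample size: "As this trial primarily assessed feasibility on RA prevention by TCM, sample size was not strictly predetermined".

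The outcomes are of another kind. Section 2.5.2: "The primary outcome is the time to the occurrence of RA". Section 2.9.2: "The primary outcomes will be compared between the two groups via the log-rank test and the Kaplan–Meier method", with superiority judged on a 95% confidence interval and two-sided tests at 0.05. Section 2.5.3 lists eight groups of secondary outcomes: RA proportions, autoantibodies, inflammatory markers, joint findings, global scores, quality of life, ultrasound and radiography. Section 2.5.4 is safety.

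On size, section 2.7 starts from 30 per group, adds 20% to reach 72, and claims power above 80%: "we assumed that RA incidence would be 20.0% in the FA group and 37.5% in the placebo group".

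Section 4 calls the study a small pilot that may not be conclusive. It then makes two claims about what the results can offer to prevention research. The first is that "any significant differences or trends in the efficacy of FA at the endpoints of this trial will provide seminal evidence". The second concerns a null finding: "even neutral results will be important revelations to the community".

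**The concern.** The objective determines what the trial must report, and here it has no outcome attached. Followed as printed, the trial ends with a log-rank P value and a set of clinical comparisons. It gives no prespecified measure of whether a larger trial could recruit, retain and assess people over 104 weeks, and no result that would count for or against such a trial.

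The efficacy comparison that takes its place is far weaker than section 2.7 says. A reader who trusts the power claim would take a non-significant result as evidence against the formulation, while section 4 encourages a favourable reading of trends. At this size neither is warranted.

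**Working it through.** **1. Objective against outcomes**

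| Possible feasibility measure | Listed as an outcome (2.5.2–2.5.4)? | Where the article touches it |
|---|---|---|
| Enrolment | No | Recruitment routes (2.3.3); online allocation (2.8) |
| Retention at weeks 52 and 104 | No | 20% dropout allowance (2.7); visits (Table 2) |
| Adherence | No | Measures to promote it (2.4.4); packaging returned (2.4.1); no row in Table 2 |
| Ultrasounds done | No | Schedule only (Table 2) |

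**2. The plan's own sample size**

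Inputs from 2.7: P₀ = 0.200, P₁ = 0.375, Zα = 1.96, Zβ = 0.84, δ = 0.15. The observed gap is ε = 0.375 − 0.200 = 0.175.

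- Numerator: (1.96 + 0.84)² × (0.200×0.800 + 0.375×0.625) = 7.84 × 0.394375 = 3.092.
- Printed denominator with margin and gap added: (0.175 + 0.15)² = 0.1056. N = 29.27, rounded up to 30. With 30 per arm this gives 80.9% power. 60 × 1.2 = 72.
- Without the margin: 3.092 / 0.175² = 101 per arm.

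So 30 per arm is reproduced only by treating the effect as 32.5 points instead of the assumed 17.5.

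**3. Power of the planned test**

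Under proportional hazards, with both rates cumulative over follow-up, HR = ln(0.800)/ln(0.625) = 0.475 and |ln HR| = 0.745. Schoenfeld: power = Φ(√events/2 × |ln HR| − 1.96).

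| Per arm | Expected events | Calculation | Power | Simulated log-rank |
|---|---|---|---|---|
| 30 | 30×(0.200+0.375) = 17.25 | Φ(1.547 − 1.96) | 34.0% | 32% |
| 36 | 36×0.575 = 20.7 | Φ(1.695 − 1.96) | 39.5% | 37% |

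The 36-per-arm row assumes no dropout at all. For 80% power, 57 events (Schoenfeld) to 62 (Freedman) are needed. At an average incidence of 0.2875, 57/0.2875 ≈ 198 evaluable participants or more.

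**4. What a neutral result would show**

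If both arms have 37.5% incidence, expected events are 60×0.375 = 22.5 or 72×0.375 = 27. The 95% CI factor around HR 1.0 is exp(1.96×2/√events):

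- 22.5 events: exp(0.826) = 2.285, so about 0.44 to 2.29.
- 27 events: exp(0.754) = 2.13, so about 0.47 to 2.13.

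**5. What 72 participants can say on retention**

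The plan's own requirement is 30 of 36, or 83.3%. Half-width: 1.96 × √(0.833×0.167/72) = 0.086, about ±9 points.

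**The case against.** **Efficacy intent is visible elsewhere.** The Introduction says the trial will explore the formulation's role in prevention, and the phrasing in 2.7 can be read as proof of concept. This stands as a reason to allow a second remedy, restating 2.1. It does not remove the contradiction, because the Introduction's aim is not made an objective and the abstract repeats feasibility.

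**The article condenses a longer protocol.** Adherence tables, screening logs and thresholds may be held elsewhere, so their absence alone is no finding. But the article prints its objective together with its primary, secondary and safety outcomes, and these disagree with each other.

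**The Discussion is hedged.** It concedes that results may not be conclusive, and its sentence on trends is not an analysis rule. Both are true. The sentence still promises more than a test with about one-third power can deliver.

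**Stronger readings to avoid.** A reader might infer that the trial can say nothing about feasibility. The text does not support that: recruitment and dropout can still be described afterwards, and what is missing is a prespecified measure and criterion. A reader might also infer that a neutral result would carry almost no information. With equal arms at 37.5%, the lower confidence limit (0.44 to 0.47) would lie close to the assumed HR of 0.475, so an effect of that size would be nearly excluded, though not quite. Nor does the mismatch require replacing the primary outcome in a trial that has been recruiting since March 2022; that would be a debatable trade.

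**Conclusion.** The point holds as a contradiction in the printed text: a feasibility objective stated three times, no feasibility outcome, and a superiority test on time to RA as the primary analysis. That test has about 34% to 40% power for the plan's own rates (32% to 37% by simulation), against a stated figure above 80% that arises only from adding the 0.15 margin to the 17.5-point difference. These figures assume proportional hazards, rates cumulative over follow-up, and no loss beyond the stated 20%.

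A non-significant result or a trend would establish neither efficacy nor its absence. The size suits feasibility better, but not sharply: ±9 points on retention will not separate values close to a threshold.

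**What to change.** Choose one of two routes.

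- **Keep the feasibility objective.** By dated amendment, made while blinded, add: enrolment rate per centre; retention at weeks 52 and 104; share of scheduled ultrasounds done; adherence from returned packaging where it can be counted. Give each a progression criterion. Tie retention to the plan's own 30 of 36 (83%), and state the ±9-point precision beside it. Keep time to RA as the main efficacy outcome, labelled exploratory and reported as HR with 95% CI.
- **Restate section 2.1 as exploratory efficacy,** so that objective and primary outcome agree.

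Under either route, replace the power claim in 2.7 with about 34–40% for the planned test. Replace the section 4 sentence with a statement that a non-significant result or trend establishes neither efficacy nor its absence, and give the expected interval for a neutral result (about 0.44–2.29 to 0.47–2.13).

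Cost: a protocol amendment whose criteria are set after enrolment began, which must be disclosed; possible extra logging, since the article describes no screening counts or dose counts; and a less prominent efficacy claim.

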### 2.2 Study design

This is a study protocol of a multicenter, double-blind, randomized controlled trial (RCT). Six centers are involved in this RCT, including the Guangdong Provincial Hospital of Chinese Medicine (GPHCM), the Guangdong Provincial Hospital of Chinese Medicine Zhuhai, the Dongguan Hospital of Guangzhou University of Traditional Chinese Medicine, The Second Affiliated Traditional Chinese Medicine Hospital of Guizhou University of Traditional Chinese Medicine, the Liaocheng Traditional Chinese Medicine Hospital, and the Inner Mongolia Hospital of Traditional Chinese Medicine. The protocol was approved by the GPHCM ethics committees (BF2021-159-01) on September 8, 2021, and study was registered in the Chinese Clinical Trial Registry on October 1, 2021^1^. We started recruitment in March 2022 and plan to finish in 2026.

### 2.3 Eligibility criteria

#### 2.3.1 Inclusion criteria

Participants must:

(1)   be aged between 18 and 75 years (inclusive) at the time of initial screening.(2)   Test positive for anti-CCP, regardless of RF status.(3)   Be present with or without arthralgia that may be accompanied by joint discomfort, such as pain or stiffness, but not synovitis.(4)   Not meet the 2010 American College of Rheumatology/European League Against Rheumatism classification criteria for RA as confirmed by a certified rheumatologist.(5)   Have no prior exposure to any DMARDs.(6)   Eligible individuals must agree to participate in the trial and sign an informed consent form.

#### 2.3.2 Exclusion criteria

Any of the following circumstances must be excluded:

(1)   A history of other rheumatic autoimmune diseases, such as Sjögren syndrome or systemic lupus erythematosus; acute or chronic infections, including hepatitis B or hepatitis C; evidence of active, latent or inadequately treated Mycobacterium tuberculosis infection; or a history of cancer.(2)   Severe diseases of the brain, lungs, liver, kidneys, cardiovascular system, or hematopoietic system or diabetes.(3)   Pregnant women, nursing mothers, or individuals with psychiatric disorders.(4)   A hemoglobin level of less than 90 g/L, a white blood cell count of less than 3.0 × 10^9^/L, or a platelet count of less than 100 × 10^9^/L.(5)   The estimated glomerular filtration rate (eGFR) of 40 mL/min or less (calculated via the method of Cockcroft and Gault).(6)   The aspartate aminotransferase (AST) or alanine aminotransferase (ALT) levels greater than 1.5 times the upper limit of the normal range.(7)   Active gastroduodenal ulcers or gastritis caused by long-term use of nonsteroidal anti-inflammatory drugs (NSAIDs).(8)   Hypersensitivity to the trial medication.(9)   Synovitis detected by ultrasound prior to the inclusion.(10)   Previous use of glucocorticoids, regardless of whether oral or topical treatment was used.(11)   Participation in other clinical trials within 4 weeks prior to screening.

#### 2.3.3 Recruitment

There are four main approaches for recruitment:

(1)   Outpatient clinics at the six centers: Physicians conduct an initial assessment of patients arriving at their clinics.(2)   Population health screening: a blood test for the anti-CCP antibody is included in the health screening service to identify people who are anti-CCP positive.(3)   News media and advertisement: Residents can volunteer for screening through newspapers, advertisements, WeChat public accounts, telephone counseling, video media, etc.(4)   Other hospitals: eligible patients will be recommended for this study.

After preliminary screening, individuals who are considered potential participants in this trial will undergo a more detailed assessment according to the inclusion and exclusion criteria. If the eligibility criteria are met, informed consent (including additional consent provisions for the collection and use of participant data and biological specimens in ancillary studies) will be provided and explained by the clinician and should be signed by the participant.

